### Recruitment and Consent

#### Patient Participants

Purposive sampling methods will be used to recruit individuals living with acquired brain injuries with impairments spanning all domains of interest. The participants will be recruited through the Ontario Workers Network and relevant rehabilitation clinics at the Ottawa Hospital. Electronic medical records will be screened to identify eligible patients, who will then be called or approached in person for consent.

#### Clinician Participants

Clinicians will be recruited from the Ontario Workers Network and relevant rehabilitation clinics at the Ottawa Hospital to participate as clinician assessors in the study. Consent will be obtained over the telephone or face to face.

### Outcomes

The virtual toolkit of assessments will include the following outcome measures: the classification of abnormality (binary variable) on the finger-to-nose test, Vestibular/Ocular Motor Screening tool, balance testing, cervical spine range of motion, saccades testing, and evaluation of effort. The procedures outlined below provide details for these outcome measures, including the methods used for evaluating the sensitivity of the virtual assessment when compared to the in-person assessment and the interrater and intrarater reliabilities of the virtual assessment.

### Procedures

#### Training

Training of the assessing clinicians on the outcome measures will occur prior to commencement of patient-participant recruitment. A previously developed training manual [22] will be used to complete the training. Training will be uniform with the goal of standardizing clinician completion of the assessments.

#### Assessments

Data collection will occur in Research Electronic Data Capture (REDCap), a secure electronic data capture application. An assessing clinician will conduct two assessments: one in person and one virtual. Both assessments will be identical consisting of all measures from the virtual assessment toolkit (see Table 1). Both assessments will be completed at the Ottawa Hospital. When possible, assessments will occur on the same day with a brief rest period in between [23,24]. The order of assessment completion (in person vs virtual) will be randomized and counter-balanced. A random-numbers table will be generated and imported into REDCap and the randomization will occur through REDCap. In addition to the assessments identified in Table 1, clinicians will document adverse events (if any) and will record findings from the assessments on a paper copy, which will be directly input into REDCap by a research team member.

For the virtual assessment, the patient participants will be located in a separate room from the assessing clinicians within the Ottawa Hospital. All patient participants will use the same computer and will be provided with technical support from a research team member as needed. The virtual assessments will be conducted in the clinical environment to standardize as many components of the assessment as possible, including computer screen, lighting, image size, and room setup. During the virtual assessment, several safety measures will be implemented: (1) a research team member will be present in the room throughout and (2) the patient participant will stand in front of a wall/bed/chair or with their back at a corner during the vestibular assessments in case of loss of balance. All the virtual assessments will occur through the Microsoft Teams platform. The study assessments will be audio/video-recorded using the record function on Microsoft Teams.

Where possible, both assessments will be completed on the same day. It is estimated that a portion (~5%) of participants may be unable to complete both the in-person and virtual assessments on the same day, either due to lack of time or inability to tolerate a second assessment as a result of symptom aggravation (eg, headaches, dizziness, nausea, sensitivity to noise and light). For these participants, the second assessment (virtual or in person) will be scheduled for completion within 1 week of the initial assessment.

Following completion of the assessments, the patient participants and clinician assessors will complete a feedback form. Participants will complete a feedback form (see Multimedia Appendix 1) related to completion of the virtual assessment, the environmental setup, and confidence in the assessment findings.

**Table 1 table1:** Outline of measures included in the virtual assessment toolkit to be completed in both in-person and virtual assessments^a^.

Domain	Measures	Documentation of findings by clinicians
Neurological examination	Coordination: finger-to-nose test	Abnormal (hesitation, tremor, over- or undershooting [25])/normal
Vestibular	VOMS^b^	Change in symptoms (≥2 point increase indicates abnormality [26]); average distance for 3 trials of near-point convergence in centimeters (≥5 cm convergence indicates abnormality [26])
Vestibular	Balance (feet together, single-leg stance, tandem stance) with eyes open and eyes closed for 20 seconds each	Abnormal (unable to complete 20-second balance [22])/normal
Oculomotor	Saccades	Abnormal (observe saccade initiation, range of motion and conjugacy, speed, accuracy, intrusions, or oscillations [27])/normal
Cervical	Range of motion (flexion, extension, right and left lateral flexion, right and left rotation)	Estimated angles for each recorded abnormality (determined by comparison to norms in people aged 20-59 years: flexion=50°-72°, extension=58°-77°, lateral flexion=37°-47°, rotation=67°-81° [28])
Effort	Rating scale	Full use of effort documented as yes or no (clinician discretion); rating scale documented from 0 (no effort) to 10 (maximum effort) (clinician discretion)

^a^For a complete presentation of the instructions used to administer the measures, see Johnston et al [22].

^b^VOMS: Vestibular/Ocular Motor Screening.

#### Observation and Rating of Audio-Video Recordings

A second clinician (rater B in Figure 1 [17]) will complete two ratings of the recording of the virtual assessment (in a randomized order for participants) at 1-month intervals. Clinicians will record findings from the assessments on paper or electronic copies, which will be input directly into REDCap by a research team member. See Figure 1 [17] for an outline of study assessment procedures.

**Figure 1 figure1:**
[figure not shown]
Assessment procedures (adapted from Russell et al [17]).

### Analysis

#### Assessments Overview

Patient and clinician participant characteristics will be descriptively analyzed. IBM SPSS (version 28) will be used to calculate the sensitivity of virtual assessments versus in-person assessments, along with the κ values (interrater and intrarater reliabilities) of the virtual assessments (see Figure 1 for comparisons).

#### Method-Comparison (Sensitivity) Analysis

The sensitivity of the virtual assessment compared to the gold-standard in-person assessment (rater A in person vs rater A virtual) will be determined, where the assessment of the uncertain classification of the measures used virtually will occur against the gold standard or “true” classification, which is the in-person assessment in this study. The findings of the initial clinician assessor (rater A) that completed the in-person and virtual assessments will be compared to determine the sensitivity of the measures administered virtually. In this case, sensitivity (true positives divided by the sum of true positives and false negatives multiplied by 100) refers to the ability of the virtual measure to identify a deficit or positive finding when the in-person measure identifies the deficit or positive finding. Values closer to 100% indicate greater sensitivity.

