**Conclusions:**

Currently, it is unknown if completing concussion assessments virtually produces similar results to the in-person assessment. This work will serve as a first step to determining the similarity of the virtual assessment to the matching in-person assessment and will provide information on the reliability of the virtual assessment.

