### Sample Size

The target sample size of this method-comparison study is 60 patient participants. For the objective of assessing the sensitivity of the virtual assessment against the gold standard of in-person assessment, with a total of 60 participants, 50 (83%) of whom are expected to have an abnormal finding, and an estimated sensitivity ranging from 77% to 96%, the two-sided 95% CI around the estimated sensitivity will have a total width ranging from 8.7% to 25.3% (or margin of error 4.4%-12.7%). For the objective of assessing interrater agreement between two clinicians conducting a virtual assessment using the κ statistic, a sample size of 60 participants achieves 80% power to detect a true κ value of 0.89 using a one-sided test at the 5% significance level, assuming that 90% of participants are classified as abnormal; κ under the null hypothesis was specified as 0.5.

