### Conclusion

This method-comparison study is an important endeavor considering the limited exploration of virtual concussion assessments in the literature despite their increasing use in practice. This study aims to determine whether virtual and in-person assessments yield similar results in terms of the identification of abnormality in common physical domains of a concussion assessment. The study will also assess the interrater and intrarater reliabilities of the virtual assessment, contributing valuable insights to the field of concussion rehabilitation.

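### Sensitivity is the only planned in-person versus virtual statistic, so virtual false positives never count, yet the article aims to conclude that the two modes give similar results

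*Protocol article*

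**What the plan says.** The first objective, in the Abstract and under Objectives, is the sensitivity of the virtual assessment with the in-person assessment as gold standard. Method-Comparison (Sensitivity) Analysis gives the formula: "sensitivity (true positives divided by the sum of true positives and false negatives multiplied by 100". The Assessments Overview lists the output as this sensitivity plus κ values for inter- and intrarater reliability of the virtual assessments.

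Under Reliability, both κ comparisons stay within the virtual mode: rater A's virtual findings against rater B's first reading of the recording, and rater B's first reading against the second. Specificity, percent agreement and an in-person versus virtual κ appear nowhere in the article.

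Sample Size states "The target sample size of this method-comparison study is 60 patient participants", "50 (83%) of whom are expected to have an abnormal finding", and "an estimated sensitivity ranging from 77% to 96" per cent.

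The intended conclusion is wider than detection. The Conclusion section says "This study aims to determine whether virtual and in-person assessments yield similar results in terms of the identification of abnormality". The Abstract's Conclusions describe a first step towards "determining the similarity of the virtual assessment to the matching in-person assessment".

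**The concern.** Two modes give similar classifications only if people who are abnormal in person are called abnormal virtually and people who are normal in person are called normal virtually. Sensitivity measures the first and is silent on the second.

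A virtual examination that over-calls abnormality could therefore report a high figure and be described as similar to the in-person examination, with nothing in the planned comparison to show otherwise. The article itself says the measures should identify problem areas accurately so that treatment can be directed (Projected Significance). False positives bear on that as much as false negatives do.

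**Working it through.** **Inputs.** N = 60, with 50 abnormal in person and so 60 - 50 = 10 normal (Sample Size, sensitivity objective). Anticipated sensitivity is 77% to 96% (same section). The formula is from Method-Comparison (Sensitivity) Analysis.

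**Notation.** a = abnormal in both modes; b = abnormal in person, normal virtually; c = normal in person, abnormal virtually; d = normal in both. Here a + b = 50 and c + d = 10.

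**1. The plan's own figure.** The article says the 95% interval "will have a total width ranging from 8.7% to 25.3% (or margin of error 4.4%-12.7" per cent. With n = 50 and a continuity-corrected Wald interval, width = 2 × [1.96 × √(p(1-p)/n) + 1/(2n)].
- At p = 0.77: 2 × (0.1167 + 0.01) = 25.3%, which matches.
- At p = 0.96: 12.9%, or 10.4% if cut at 100%. Plain Wald gives 10.9%, Wilson 12.4% and exact 13.2%. None gives 8.7%.
- At p = 0.97, cut at 100%: 8.7%.

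The lower width is thus not reproduced at the stated 96%. That is a separate matter and does not affect what follows. The calculation does confirm that precision was planned on the 50 abnormal participants only.

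**2. Which cells are used.** Sensitivity = a/(a + b). Cells c and d do not appear.

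**3. What a sensitivity of 96% leaves open.** Take a = 48, b = 2, the top of the anticipated range. Agreement = (a + d)/60. Chance agreement = [(a + b)(a + c) + (c + d)(b + d)]/3600. κ = (agreement - chance)/(1 - chance).

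| Specificity d/10 | Sensitivity | Agreement | Chance agreement | κ |
|---|---|---|---|---|
| 0/10 | 96% | 48/60 = 80.0% | (50×58 + 10×2)/3600 = 0.811 | -0.06 |
| 5/10 | 96% | 53/60 = 88.3% | (50×53 + 10×7)/3600 = 0.756 | 0.52 |
| 10/10 | 96% | 58/60 = 96.7% | (50×48 + 10×12)/3600 = 0.700 | 0.89 |

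The planned statistic is the same in all three rows.

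**4. Limiting case.** If everyone is called abnormal virtually, b = 0 and sensitivity = a/a = 100% whatever the share of abnormal participants. At 50/10, specificity is 0/10, agreement 50/60 = 83.3%, chance agreement (50×60 + 10×0)/3600 = 83.3%, and κ = 0.

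**5. Do the planned κ values fill the gap?** No in-person rating enters either of them. If only one rater over-calls on the virtual session, interrater κ falls. If both over-call alike, it need not fall. If both call everyone abnormal, agreement and chance agreement are both 1 and κ is 0/0, which is undefined.

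**6. Precision of specificity if it is added.** With 10 normals, 9/10 gives an exact (Clopper-Pearson) 95% interval of 55.5% to 99.7%, and 10/10 gives 69.2% to 100%.

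**The case against.** The strongest reply is that sensitivity is a declared choice. The objective names it, the sample is purposively enriched for deficits because concussion examinations are often normal, and the sample size is built on it. Objective and analysis therefore agree. The article also describes itself as a first step giving preliminary information, and a fuller analysis plan may exist.

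Most of this stands, and it narrows the point: the mismatch is between the analysis and the similarity conclusion. It does not remove the mismatch. The article fixes the objective, statistic, formula and output, and then states a wider aim. Preliminary status affects how firm an answer can be, not which cells of the table it draws on.

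A reader might infer several stronger things that the documents do not support:
- **That the high expected share of abnormal findings causes the problem.** It does not, since calling everyone abnormal gives 100% sensitivity at any share. The share matters only because it leaves few normals.
- **That 83% to 90% is one stated range.** The 83% belongs to the sensitivity objective. The 90% ("assuming that 90% of participants are classified as abnormal") belongs to the interrater κ calculation. The article does not say whether either applies per measure.
- **That over-calling on video is likely.** The article gives no such evidence. It describes trained assessors, defined criteria and a standardised set-up.
- **That over-calling would raise the reported figure.** False positives among in-person normals leave sensitivity unchanged. It rises only if a looser threshold also turns false negatives into true positives.
- **That no planned statistic could ever react.** Over-calling by one rater alone would lower interrater κ.

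**Conclusion.** The concern holds in this form: the planned in-person versus virtual comparison takes no account of virtual false positives, so it cannot by itself support a conclusion that the two modes yield similar results. It can support a statement about how often abnormalities found in person are also found virtually.

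Under the article's own 50/10 split, a reported sensitivity of 96% is consistent with anything from slightly worse than chance agreement (κ -0.06) to very high agreement (κ 0.89). The exact range depends on that split, and individual measures may have a different mix. The underlying point is algebraic and depends on no assumed failure of video.

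The Abstract's Methods base sensitivity on the second clinician's reading of the recording, whereas the Analysis section uses rater A's own virtual findings. That discrepancy needs reconciling separately. Sensitivity is the only mode-comparison statistic under either description.

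**What to change.** For each measure, report the full in-person versus virtual 2x2 table, with sensitivity and specificity and their 95% confidence intervals. An in-person versus virtual κ is a useful optional addition. State in the Analysis section that any conclusion about similarity will rest on sensitivity and specificity together.

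Alternatively, keep sensitivity as the only statistic and reword the Conclusion and the Abstract's Conclusions so that they claim only detection of abnormalities found in person.

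The first option needs no new participants, visits or ratings, because both modes are already rated in each participant and all four cells exist. Its small downside is that specificity will be imprecise for measures with few in-person normals. At the planned 10, even 10/10 leaves a lower limit of 69.2%, so the report should state this and not treat a high point estimate as firm evidence of similarity.

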#### Reliability

To calculate the interrater reliability of the virtual assessment, the findings of rater A (virtual assessment) will be compared to the findings of rater B_1_ (initial observation of the virtual assessment recording). To determine the intrarater reliability of the virtual assessment, the findings of rater B_1_ (initial observation of the virtual assessment) will be compared to the findings of rater B_2_ (second observation of the virtual assessment) approximately 1 month after the initial observation. Estimates of reliability will be calculated using the κ statistic (classification of abnormal vs normal) for all measures included in the toolkit.

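### Convergence distance, symptom change, neck angles and effort are recorded as numbers but analysed only as normal/abnormal, so a systematic virtual offset in them is not quantified

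*Protocol article*

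**What the plan says.** The Outcomes section sets one scale for the whole toolkit: "the classification of abnormality (binary variable"), applied to all six measures.

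Table 1 (under Assessments) shows that several of these start as numbers:

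- Symptom change on the vestibular/ocular screen, in points: "Change in symptoms (≥2 point increase indicates abnormality").
- Convergence distance: "average distance for 3 trials of near-point convergence in centimeters (≥5 cm convergence indicates abnormality").
- Cervical range of motion, six movements: "Estimated angles for each recorded abnormality (determined by comparison to norms in people aged 20-59 years").
- Effort, in addition to a yes/no judgement: "rating scale documented from 0 (no effort) to 10 (maximum effort").

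Finger-to-nose, balance and saccades are documented directly as normal or abnormal.

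The Method-Comparison (Sensitivity) Analysis section compares rater A in person with rater A virtual. It names one statistic, sensitivity, and treats values nearer 100% as better. The Reliability section compares rater A virtual with rater B's first viewing of the recording, and rater B's first viewing with the second: "Estimates of reliability will be calculated using the κ statistic (classification of abnormal vs normal) for all measures included in the toolkit". The analysis overview lists the same two statistics. No mean difference, limits of agreement, intraclass correlation, weighted κ or specificity is named.

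**The concern.** The design is a method comparison, and for four of the recordings the data would show directly how far a virtual reading sits from an in-person one. Once cut into normal and abnormal, and summarised by sensitivity alone, a consistent offset is not measured, and its effect depends on its direction:

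- If virtual readings lean towards abnormal (angles read too small, convergence read too far), more of the in-person abnormals are also called abnormal virtually, so sensitivity goes up. The cost falls on patients who were normal in person, and sensitivity does not use them.
- If virtual readings lean towards normal, sensitivity drops, but it may stay in the range the plan already expects and would not stand out.

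The reliability κ does not fill the gap. Both comparisons are virtual against virtual, so an offset shared by all virtual readings largely cancels.

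At stake is whether a good sensitivity figure for these measures reflects close readings or a biased scale.

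**Working it through.** **The plan's own figure.** For the interrater κ test (κ 0.89 against 0.5, 90% abnormal, one-sided 5%, 80% power), the large-sample standard errors of κ with equal marginals of 0.90 are 1.443/√N under the null and 0.771/√N under the alternative. Then N = ((1.645 × 1.443 + 0.842 × 0.771) / 0.39)² ≈ 60.1, so the stated 60 reproduces. The binary reliability analysis is sized as described and is not disputed.

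**Inputs for the illustration.** From the article: 60 patients; 50 of 60 (83%) expected abnormal; planned sensitivity 77–96%; lower end of the rotation norm 67°; 39 patients assessed by May 2024. Assumed, because the article gives no such figures: true rotation SD 10°, reading error SD 4° in each mode, normal distributions, and the 83% applied to this single measure.

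**Model.** In-person reading I = T + e₁; virtual reading V = T + b + e₂; abnormal if below 67°. The SD of a reading is √(10² + 4²) = 10.77°. Setting P(I < 67) = 0.833 gives a mean of about 67 − 0.967 × 10.77 ≈ 56.6°. The correlation of I and V is 100/116 = 0.86. Sensitivity = P(I < 67 and V < 67) / P(I < 67). Specificity is the same ratio for readings of 67° or more.

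| Virtual offset b | Sensitivity | Specificity (not planned) |
|---|---|---|
| −5° (under-reads) | 99% | 39% |
| 0 | 94% | 69% |
| +5° (over-reads) | 81% | 90% |

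With 50 abnormal and 10 normal in person, the −5° offset moves detected abnormals from about 47 to 49 of 50, and false alarms from about 3 to 6 of 10.

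**Dependence on the share abnormal.** With 50% abnormal (mean 67°), offsets of −5°, 0 and +5° give sensitivity 96%, 83% and 60%, and specificity 60%, 83% and 96%. The directions are unchanged, but over-reading would then fall below the planned range.

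**Convergence distance.** Assumed mean 8.87 cm, SD 4 cm, error SD 1 cm, with the 5 cm cut from Table 1 (about 83% abnormal). Offsets of 0, +1 and +2 cm give sensitivity 96%, 99% and nearly 100%, with specificity 80%, 62% and 43%. Offsets of −1 and −2 cm give sensitivity 90% and 81%. The κ between two virtual ratings stays between 0.90 and 0.92 throughout (second rater's added error SD assumed 0.5 cm).

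**Precision of a numeric comparison.** The SD of paired angle differences is √(4² + 4²) = 5.66°.

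- 60 pairs: mean difference ±1.96 × 5.66/√60 = ±1.4°; each limit of agreement ±1.96 × 5.66 × √(1/60 + 1.96²/(2 × 59)) = ±2.5°.
- 21 pairs (60 − 39): ±2.4° and ±4.2°.

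Free of any assumed SD, 60 pairs give the mean difference to about ±0.26 SD of the differences and each limit of agreement to about ±0.44 SD.

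**The case against.** The strongest reply is that the declared question is classification. The Conclusion asks whether the two modes give similar results in identifying abnormality, and the binary analysis answers in those terms. That stands: the binary analysis should remain primary, and the numeric analysis is an addition. A reader might infer that the study fails its central question; the article's own framing does not support this.

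Second, the flattering effect of under-reading comes largely from reporting sensitivity without specificity, and the full 2×2 table would expose it. This is also right. Specificity would show that something is off, though not by how many degrees or centimetres, and it is not planned either. Nor is an offset wholly invisible as planned, since over-reading lowers sensitivity.

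Third, a reader might assume that every numeric analysis could be run on data already held. For angles this is not assured. Table 1's wording can be read as keeping an angle only where a movement is abnormal, and 39 of 60 patients had been assessed by May 2024. The ±1.4° precision may then not be available.

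Fourth, a condensed article may leave supplementary summaries to the full plan. That would carry weight if the article were silent. It instead fixes a binary outcome and states κ on abnormal versus normal for all measures.

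**Conclusion.** The point holds for convergence distance, symptom change and effort, and for neck angles as far as paired values exist. It does not apply to finger-to-nose, saccades or balance. For the numeric measures the plan names no statistic that estimates a systematic virtual offset, and the one virtual-versus-in-person statistic it names improves when that offset is towards abnormal.

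Under the assumed values at about 83% abnormal, a 5° under-reading takes sensitivity from 94% to 99% while specificity drops by 30 points, and a 5° over-reading leaves sensitivity at 81%, within the planned range. The sizes rest on the assumed SD, error SD and share abnormal; the directions do not. The binary results remain usable, so this is an improvement that should be made rather than a flaw that invalidates the study.

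**What to change.** 1. Keep sensitivity and κ on the normal/abnormal classification as the primary analysis.
2. Add a secondary analysis of rater A in person against rater A virtual: mean virtual minus in-person difference with 95% limits of agreement and their confidence intervals, for convergence distance and for angles where both readings exist.
3. For rater A virtual against rater B's first viewing, and for rater B's two viewings, add intraclass correlations with 95% confidence intervals. For symptom change and the 0–10 effort rating, use weighted κ or the intraclass correlation.
4. State whether angles are recorded for all movements or only for abnormal ones. If only abnormal ones, record all from now on, limit the angle agreement analysis to participants with paired values, and report the wider precision (about ±2.4° for the mean with 21 pairs, against ±1.4° with 60, under the assumed SD).

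The cost is a paragraph of analysis text and a few tables. No additional patients are needed. The only possible change to conduct is fuller entry of angles, which cannot recover values not written down for participants already assessed.
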